## Abstract

**Background:**

The etiology of interstitial lung diseases (ILDs) is varied. Early diagnosis and a specific pathological type could significantly improve the prognosis. Mostly, it is difficult to make the etiology diagnosis of ILD through traditional biopsy methods. It will be of great significance to explore an effective biopsy method.

**Methods:**

The prospective study was designed to evaluate the diagnostic value of transbronchial lung cryobiopsy (TBCB) combined with rapid on-site evaluation (ROSE), compared with conventional transbronchial lung biopsy (TBLB), in a large sample of ILD patients. All patients enrolled will undergo both TBLB and TBCB procedures. The study will observe the differences in the diagnostic efficiency of pathological typing and incidence of operation-related complications between TBCB and TBLB. Besides, it will analyze the relationship between the time of biopsy and the incidence of complications, the relationship between freezing time, size of specimen, and complications. And it will evaluate the consistency of pathological, clinical, and radiology.

**Discussion:**

It may be the first time that ROSE technique will be used in the diagnosis of ILD. The results of this study will clarify the value of TBCB in the diagnosis of ILD and confirm its safety and effectiveness, which is expected to significantly improve the efficiency of diagnosis in ILD patients.

*Trail registration*: The trial was registered on the Chinese Clinical Trial Registry website (http://www.chictr.org.cn/showproj.aspx?proj=57834) (Registration number: ChiCTR2000035492).

## Background

Interstitial lung diseases (ILDs) are a group of diffuse diseases that mainly involve the pulmonary interstitial and alveolar cavity. They are characterized by progressive dyspnea, diffuse infiltrating shadows in the lungs, hypoxemia, and restrictive ventilation disorder [1, 2]. The etiology of ILD is varied, and the majority of patients with idiopathic pulmonary fibrosis (IPF) lack effective treatment, with a median survival time of 3 years [3]. If patients with ILD can be diagnosed early and have a specific pathological type, individualized treatment measures could significantly improve the prognosis. At present, the diagnosis of ILD mostly requires high resolution computerized tomography (HRCT) and bronchoalveolar lavage (BAL), lung biopsy and pathological examination by various means if necessary. The common methods of lung biopsy are transbronchial lung biopsy (TBLB), X-ray/ultrasound-guided percutaneous lung biopsy, and surgical lung biopsy (SLB). However, due to the small size of specimen by TBLB and percutaneous lung biopsy, and the extrusion and deformation of tissues, they hardly meet the needs of ILD pathological diagnosis. SLB is still the most effective biopsy method at present, but SLB may increase the risk of acute exacerbation and infection rate of ILD patients, and the mortality within 30 days is about 3–4% [4, 5]. Transbronchial lung cryobiopsy (TBCB) is a technique inserting a probe into a distal bronchial or pulmonary lesion through a bronchoscope and tearing the surrounding lung tissue to obtain the target tissue. Rapid on-site evaluation (ROSE) is a technique used when specimens are collected by puncture, biopsy, brush, etc., Related personnel are on site to conduct a rapid evaluation of the satisfaction of the obtained specimen, to make a preliminary diagnosis, priority strategy, and feedback for the next step. At present, ROSE is mainly used in the diagnosis or differential diagnosis of solid malignant tumors, tuberculosis, fungal infections, sarcoidosis, and other pulmonary diseases, but rarely applied in the diagnosis of ILD.

The prospective study was designed to evaluate the diagnostic value of TBCB combined with ROSE, compared with conventional TBLB combined with ROSE in a large sample of ILD patients. It is the first study to apply ROSE technique in the diagnosis of ILD. The results are expected to establish a new, efficient and fast diagnostic method and may promote the standardization of the pathological sampling standards and pathological diagnostic standards of ILD.

## Methods

### Study objects

According to the literatures, the estimated sensitivity rates of TBCB and TBLB methods were 80% and 60%, respectively. The estimated prevalence rate of the target subjects is 50%. Using McNemar test with PASS software to calculate the sample size, when the value of ɑ was 0.05, the sample size was 122 cases. And totally 146 hospitalized patients with diffuse lung disease were intended to be enrolled in the study with the amplification of 1.2 times. The specific criteria are as follows:Inclusion criteria

(a) ILD patients with unknown reasons (more than 18 years old), have the necessity to undergo TBCB for the diagnosis; (b) Hospitalized patients need to complete arterial blood gas analysis, blood routine, blood coagulation routine, liver and kidney function, electrocardiogram, immunology examination, chest HRCT, and other examinations; (c) Good compliance and can be coordinated with this study; (d) After being fully informed of the purpose and method of the study, the patients are willing to participate in the study and sign the informed consent.

(2)Exclusion criteria

(a) Do not agree to participate in the study; (b) Have participated in other studies that could affect the observation of this study; (c) Patients who fail to complete the examination required for admission before TBCB or TBLB; (d) Chest HRCT showed non-interstitial lung disease; (e) Any conditions deemed unsuitable for inclusion by the investigators;

(3) Elimination criteria

(a) Patients who do not meet the inclusion criteria or who meet the exclusion criteria after enrollment; (b) After enrollment, patients have poor compliance and could not cooperate with the observers;

(4)Withdrawal criteria

Patients who meet the inclusion criteria and fail to complete the study for some reasons, including patients who voluntarily withdraw and are determined to withdraw by the researchers.

(5)Study end pointsa. Primary end point: The differences in diagnostic efficiency and incidence of operation-related complications between TBCB and TBLB.b. Secondary end point: Analyze the relationship between the time of biopsy and the incidence of complications; the relationship between freezing time, size of specimen and complications; The histopathological results will be handled in a multidisciplinary meeting, to analyze the consistency of pathological, clinical, and radiology.

The research process is shown in Fig. 1.

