***Collection of clinical data***

Collect relevant information about the operation, including anesthesia method, anesthesia complications, time of TBCB, time of TBLB, freezing time, and operation time;Specimens’ information, including the number and size of specimens, ROSE results, and pathological results;Complications caused by the operation, including bleeding, pneumothorax, infection, and acute exacerbations caused by the operation, as well as the delayed complications mentioned above during the 3 days of follow-up after the operation.Collecting adverse events in the study:

iii.a. Adverse event (AE): Any adverse medical event that occurs during the observation period of a patient during the study, which does not necessarily imply a causal relationship with the procedure.iv.b. Serious adverse event (SAE): An adverse event meeting one or more of the following criteria is considered as SAE, such as death; life threat; persistent or severe disability or permanent loss of function; hospitalization or prolonged stay due to AE; leading to congenital malformation.v.c. Severity classification of adverse events: mild——uninduced or only causing mild discomfort, not affecting daily life and not requiring clinical management; moderate——active narration, affecting daily life, but tolerating, requiring clinical general management; severe——having objective manifestation that cannot be tolerated, surely affecting daily life, needing rest in bed and active clinical treatment.vi.d. Relationship between adverse events and operation: it can be divided into five levels: ① definitely relevant, ② probably relevant, ③ possibly relevant, ④ probably irrelevant, and ⑤ definitely irrelevant. ①, ②, ③ are considered as operation-related adverse events.

(5) Severity of bleeding

Grade 0: no bleeding; Level 1: bleeding that can be stopped by negative pressure suction without other hemostatic measures; Level 2: bleeding that requires local injection of frozen saline, epinephrine, or balloon closure; Level 3: severe bleeding that beyond endoscopic control, resulting in hemodynamic and respiratory instability, requiring vascular intervention or surgical hemostasis, or requiring admission to intensive care unit (ICU).

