About the safety of TBCB, it was reported that there were no significant differences in the incidence of pneumothorax, bleeding, and bleeding severity compared with conventional TBLB [20, 21]. Yarmus et al. [22] reported for the first time that TBCB was used to evaluate 11 patients after lung transplantation under a soft microscope and achieved satisfactory results without serious complications. The CHILL study [23] reported that TBCB was associated with mild bleeding (grade 1 bleeding that requiring suction to clear) in 56.2% of patients, but only 16 cases were included in the study. These studies indicated that TBCB had good safety and efficacy in ILD, but they were all retrospective studies with small samples, and prospective studies with large samples are urgently needed in clinical practice to evaluate the diagnostic value of TBCB in ILD.

ROSE is a rapid cytological interpretation technique which accompanies sampling in real time during diagnostic interventional operations. In the sampling of the target sites, under the premise of almost no loss of tissue specimen, part of the sample is printed on the slides to make a cytological substrate, quickly stained and immediately interpreted with a special microscope integrated with clinical information. As a cell carrier, ROSE has the following functions: evaluation quality of the samples, guidance intervention means of operation in real time, forming the preliminary diagnosis or narrowing the scope of differential diagnosis, optimization the processing scheme of the target specimen, analyzing and predicting the outcomes of the disease combined with all clinical and cytological information [24]. However, ROSE has not been applied in ILD at present.

It is a prospective and self-controlled study to evaluate the diagnostic value of TBCB/TBLB combined with ROSE technology in a large sample size of ILD patients. In addition, it is the first time that ROSE technique was used in the diagnosis of ILD. The results of this study will clarify the value of TBCB in the diagnosis of ILD and confirm its safety and effectiveness, which is expected to improve the efficiency of diagnosis and improve the prognosis of ILD patients.

Abbreviations: TBLB, transbronchial lung biopsy; TBCB, transbronchial lung cryobiopsy; ROSE, rapid on-site evaluation.

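### Complications are half of the primary endpoint but did not enter the sample size and are tested only for a difference, so the trial cannot confirm the safety of TBCB; it can estimate a complication rate

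*Protocol article*

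**What the plan says.** All places are in the protocol article.

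- **Study objects, item (5).** The primary endpoint has two parts, given without ranking: "The differences in diagnostic efficiency and incidence of operation-related complications between TBCB and TBLB".
- **Study objects, sample size.** The inputs are diagnostic: "the estimated sensitivity rates of TBCB and TBLB methods were 80% and 60%, respectively", a prevalence of 50% and an alpha of 0.05. The method is described as "Using McNemar test with PASS software to calculate the sample size". The result is 122, multiplied by 1.2 to give 146. No complication rate is used.
- **Process of TBCB/TBLB.** Every patient has both procedures. TBLB comes first and TBCB follows at the same site in the same session. Bleeding and pneumothorax are recorded after each of the two.
- **Collection of clinical data.** Bleeding, pneumothorax, infection and acute exacerbation are collected, "as well as the delayed complications mentioned above during the 3 days of follow-up after the operation".
- **Statistical analysis.** Counts are given as cases and percentages and compared by chi-square tests. No margin and no interval for the difference is mentioned.
- **Conclusion foreseen.** The abstract says the study will "confirm its safety and effectiveness". The closing paragraph of the Discussion repeats it: "confirm its safety and effectiveness, which is expected to improve the efficiency of diagnosis".

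**The concern.** A confirmatory safety statement needs a design that can rule out a meaningful excess of complications. This one was sized for a different question, and its only stated comparison asks whether the two rates differ. If that test is not significant, the data may be compatible with equal rates, with a doubling, or with both.

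The risk of misreading is visible in the article. The Discussion cites earlier reports of no significant difference in pneumothorax and bleeding between TBCB and TBLB, and then says that the studies indicate good safety, although it calls them small. The same step taken with this trial's result would present missing evidence as reassurance, and clinicians would rely on it when choosing between the two techniques.

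**Working it through.** **1. The plan's own figure.** The usual paired formula is n = [z_a·√ψ + z_b·√(ψ − d²)]² / d², divided by the prevalence. Here d = 0.80 − 0.60 = 0.20, the prevalence is 0.50, and ψ is the proportion of discordant pairs. Power, sidedness and ψ are not stated, so 122 cannot be reproduced uniquely, but it can be reached:

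- One-sided, 90% power, ψ = 0.30: (1.645·√0.30 + 1.282·√0.26)² / 0.04 = 60.4, so 61, and 61 / 0.5 = 122.
- Two-sided, 80% power, ψ = 0.35, unpooled variance: (1.960 + 0.842)² · 0.31 / 0.04 = 60.8, so 61, and again 122.

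122 × 1.2 = 146.4, which matches 146. The figure is not shown to be wrong. Every input to it is diagnostic.

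**2. Power for complications.** The article gives no pair of complication rates, so the rates below are assumptions. Outcomes are taken as independent within patients and the test is two-sided at 0.05. For 5% (TBLB) against 10% (TBCB):

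- Discordant cells: 0.10·0.95 = 0.095 and 0.05·0.90 = 0.045, so ψ = 0.14 and d = 0.05.
- Normal approximation at 122: Φ[(0.05·√122 − 1.96·√0.14) / √(0.14 − 0.0025)] = Φ(−0.49) = 31%. At 146 it gives 36%.
- Summing the large-sample McNemar test over all possible outcomes gives 32% and 38%. The table uses this method.

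| Assumed TBLB vs TBCB rate | 122 pairs | 146 pairs |
|---|---|---|
| 5% vs 10% | 32% | 38% |
| 10% vs 20% | 60% | 67% |
| 15% vs 30% | 80% | 87% |
| 28% vs 56% | over 99% | over 99% |

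The exact McNemar test is lower: 24% and 29% for the first row, 52% and 61% for the second.

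**3. Sensitivity to overlap.** For 5% against 10%, if 2% of patients have the complication with both procedures, power is 37.5% and 45.1% (exact test 29% and 36%). With 4% having both, close to the maximum of 5%, it is 57% and 66% (exact 43% and 54%). A doubling from 5% is thus missed more often than not, except when overlap is very high.

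**4. What an interval would show.** If both rates were 5%, the half-width of the 95% interval is 1.96·√(2·0.05·0.95 / n), which is 5.5 points at 122 and 5.0 at 146. Even with no observed difference, the upper limit would reach an excess of about 5 points, which is a doubling.

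**5. What a safety claim would need.** With the same assumptions and 80% power, detecting 5% against 10% takes 438 pairs. Excluding a 5-point excess when both rates are 5% takes 299 (one-sided 0.025). Both exceed 146.

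**The case against.** The best defence is that this is a condensed article. A success rule, a multiplicity rule and the exact paired test may stand in an analysis plan that is not shown, and the sentences about confirming safety are discussion prose and not a decision rule. The first part stands, and the absence of such rules is not held against the article. It does not rescue the conclusion, because the basis of the sample size and the conclusion to be drawn are both stated here, and an analysis plan cannot alter what the trial was sized for.

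Four stronger readings are tempting and are not supported.

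- **That a real doubling would usually be missed.** This holds only for low rates. The single TBCB complication rate in the article is 56.2% mild bleeding, from a study of 16 cases. If such bleeding counts, a doubling from 28% would almost certainly be detected.
- **That the error rate rises to 9.75%.** The figure is 1 − 0.95² and needs two tests at 5% with either one counting as success. The article states neither. Alpha appears only in the sample-size sentence, and safety and effectiveness read naturally as a joint claim, which brings no such inflation.
- **That surgical biopsy is the safety benchmark.** The Background does say "the mortality within 30 days is about 3–4" per cent, but as motivation. The comparator in the endpoint, and in the Discussion of safety, is TBLB. A day-30 check to match the surgical figure would answer a comparison that the plan does not make. Its events could not be assigned to TBLB or TBCB either.
- **That deaths after day 3 are never counted.** The 3-day window is attached to the listed delayed complications. Death is a serious adverse event, and adverse events are collected over an observation period whose length the article does not give.

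**Conclusion.** The concern holds in a limited form. Complications are part of the primary endpoint, the sample size does not consider them, and the only stated comparison is a test of difference. A claim that safety has been confirmed therefore does not follow from this design.

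For complications near 5%, power to see a doubling is about 32% to 38%, so a non-significant result would be likely even if the harm were real. Power rises to 60–67% from a base of 10% and to 80–87% from 15%. These figures rest on assumed rates, independence within patients, and a paired large-sample test. If the chi-square test were run as an ordinary unpaired one, the power would differ, but the logical gap would remain.

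The finding concerns what may be concluded. It does not show that 122 is wrong or that TBCB is unsafe. Rates can still be reported descriptively, and a large excess would be detected.

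**What to change.** 1. Keep diagnostic yield as the endpoint that carries the confirmatory test.
2. Report the peri-procedural complications recorded separately after TBLB and after TBCB (bleeding, pneumothorax) as rates, with the paired TBCB minus TBLB difference and its 95% confidence interval. State that no inference of safety will be drawn from a non-significant p-value.
3. Report delayed complications over the 3 days descriptively for the combined session. Both procedures are done at the same site in one session, so a later infection or exacerbation cannot be attributed to one of them.
4. In the abstract and the Discussion, replace the safety part of "confirm its safety and effectiveness" with a statement that the trial will estimate the complication rate of TBCB.

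The cost is wording in the endpoint, analysis and conclusion sections. There are no extra patients, visits or procedures. The downside is a less assertive safety claim. The Trial status section reports one patient enrolled, so at that point the change could still be made before almost all data exist.

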### Process of TBCB/TBLB

The patients enrolled will undergo both TBLB and TBCB procedures.

Tracheal intubation, mechanical ventilation, and vital signs monitoring

Sedation and analgesia. Place the bite and No. 8 tracheal catheter under the guidance of a soft bronchoscope. When the distal end of the catheter is located in the middle and lower part of the trachea, the catheter will be fixed. A monitor will monitor the vital signs.

(2)Placement of guide wire

Insert the soft bronchoscope via the nose, enter the trachea through the glottis from the trachea catheter, empty the capsule, and then enter the bronchus. Place the guide wire into the bronchus of the intended biopsy segment through the bronchoscope working passage, and exit the bronchoscope after the catheter is in its place. Fill the capsule and fix the guide wire, and then the guide wire will be strengthened by the respiratory therapist who is responsible for mechanical ventilation so that it will not displace.

(3)Placement and testing balloon

When the soft bronchoscope enters the airway through the tee and tracheal catheter, the assistant will send the balloon via the guide wire into the bronchial opening of the proposed biopsy segment or lobe. The balloon will be filled with air under direct vision and adjusted to completely close the bronchial opening of the proposed biopsy segment or lobe, and it is appropriate to remember the amount of air injected.

(4)TBCB/TBLB

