When the endotracheal intubation is connected to the ventilator or high-frequency ventilation, bronchoscopy will be performed. First, conventional TBLB will be performed with biopsy forceps under the guidance of X-ray, and biopsies will be performed through different segmental bronchi 2 or 3 times in general. The biopsy specimens will be checked by pathologists and performed ROSE on site to guarantee the quality to continue the biopsy. After the biopsy, X-ray fluoroscopy will be performed to check whether there is pneumothorax, and the size of biopsy specimens, bleeding, pneumothorax and operation duration will be recorded. Then, TBCB will be performed at the same site. Freezing probes will be sent to the biopsy site through a bronchoscope work channel with positioning. The bronchoscope and cryogenic probe will be pulled out after refrigeration at a distance of 1 ~ 2 cm away from the pleura for 3 ~ 4 s. Take the biopsy specimen off after thawing. The bronchoscope will reenter into the bronchial to check for bleeding. Biopsy is usually done 2 ~ 3 times. Figure 2 shows the lung tissue obtained by TBCB. Biopsy specimens will be checked by pathologists and will be performed ROSE on site to guarantee the quality for further biopsy. After the biopsy, X-ray fluoroscopy will be performed to check for pneumothorax, and size of the biopsy specimen, bleeding, pneumothorax condition and operation duration will be recorded. In both operations, the next biopsy will be performed in the absence of significant bleeding and pneumothorax. To do another site of biopsy, insert a guide wire into the balloon again, and guide the balloon into the new segment by clamping the guide wire with biopsy forceps, and repeat the preceding process. After the biopsy, mechanical ventilation and tracheal intubation will be removed when the patient regains consciousness, and the patient will be sent back to the ward for monitoring and observation for 4–6 h.

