### Statistical analysis

The original data will be uniformly stored in the paper version of the case report form, and the electronic data will be single-path input and checked by two researchers. The database will be input to Excel software and will be statistically analysed with SPSS 25.0 software. The measurement data of normal distribution will be expressed as X ± S, and the measurement data of skewness distribution will be expressed as M (P25, P75). The Mann-whitney U test will be used for comparison. Enumeration data will be expressed as cases and percentages, and chi-square tests will be used for comparison.

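### The secondary analysis of biopsy time against complications is open to reverse causation, because immediate bleeding or pneumothorax can itself lengthen or shorten the recorded duration

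*Protocol article*

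**What the plan says.** All places are in the protocol article.

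- **Study objects, item (5), among the secondary aims:** "Analyze the relationship between the time of biopsy and the incidence of complications; the relationship between freezing time, size of specimen and complications".
- **Process of TBCB/TBLB, design:** "The patients enrolled will undergo both TBLB and TBCB procedures", with forceps biopsy first and cryobiopsy then at the same site. For TBLB, "biopsies will be performed through different segmental bronchi 2 or 3 times in general"; for TBCB, "Biopsy is usually done 2 ~ 3 times".
- **Same section, continuation:** "In both operations, the next biopsy will be performed in the absence of significant bleeding and pneumothorax".
- **Same section, recording:** after cryobiopsy and fluoroscopy, "size of the biopsy specimen, bleeding, pneumothorax condition and operation duration will be recorded". The forceps step has a matching instruction. After each freeze the bronchoscope goes back in to look for bleeding.
- **Same section, freezing:** "refrigeration at a distance of 1 ~ 2 cm away from the pleura for 3 ~ 4 s".
- **Collection of clinical data:** the times listed are those of TBCB, of TBLB, of freezing and of the operation. No start or stop points are given, and no event-onset time is listed. Level 2 bleeding is defined by the need for extra local haemostatic measures. Complications also include infection, acute exacerbation and delayed events over 3 days.
- **Statistical analysis:** "The Mann-whitney U test will be used for comparison" for measurement data, and chi-square tests for counts. Neither test is tied to this end point, and no unit of analysis is given.

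**The concern.** An analysis that relates time to complications is informative only if the time was accrued before the complication. Here the two are entangled by design. A Level 2 bleed is by definition one that needed additional steps, and these take time inside the procedure. A significant bleed or pneumothorax can also prevent the next biopsy and so cut the procedure short. Duration is then written down alongside the events. Depending on which mechanism dominates, the analysis could show that longer procedures go with more complications, or with fewer, when duration has no effect at all.

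This matters beyond one table. The Background hopes that the results will help standardise pathological sampling, so an artefact about procedure time could be carried into practice. Part of the problem also lies in data collection: if only a total duration is held, no later model can separate time before the event from time caused by it.

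Two related points bear on the same end point. The freezing exposure varies over only one second. Freezing time and specimen size arise for each biopsy, whereas the named tests assume independent observations.

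**Working it through.** **The plan's own figure.** None is given for this end point. The sample size of 122 (122 × 1.2 = 146.4, enrolled as 146) belongs to the primary comparison and is not disputed. It serves below only as a convenient N.

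**1. Duration: illustration under assumed inputs.** Assumptions, none from the document: duration is normal with mean 20 and SD 6 min, there are 20 patients with an event and 102 without, duration has no effect on events, and an event shifts the recorded duration by a constant c.

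Normal approximation for Mann-Whitney at two-sided 5%:
- standard error in SD units = √(1/20 + 1/102) = 0.2445
- z = (c/6)/0.2445 × √(3/π), with √(3/π) = 0.977
- rejection probability ≈ Φ(z − 1.96)

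| c (min) | z | Approximation | Simulation |
|---|---|---|---|
| 0 | 0 | 5% (nominal) | about 5% |
| +2 | 1.33 | 26% | 28% |
| +3 | 2.00 | 52% | 50% |
| +5 | 3.33 | 91% | 91% |

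Simulated shortening gives 51% for −3 min and 91% for −5 min. With other assumptions (30 ± 8 min, 20% with an event, N = 122) the rejection rate is 35%, 75% and 100% for +3, +5 and +10 min, and 74% for −5 min. Under either set, a shift of a few minutes is enough to produce a false association, and its sign follows the sign of the shift.

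**2. A tempting repair that fails.** One could replace duration by time to first complication in patients with an event, and by time to last specimen in the others. That truncates exposure only in patients with events. If events fall uniformly between 30% and 100% of the procedure, the mean fraction is (0.30 + 1.00)/2 = 0.65. With a 20 min mean, 20 × 0.65 = 13 min is then compared with 20 min although there is no effect. Under the first set of assumptions, 99.6% of simulated trials reject.

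**3. Freezing time.** Within a 1 s window the SD is at most 0.5 s (half the values at each end), and 1/√12 = 0.29 s if uniform. Simulated power at N = 122, one value per patient and an assumed 20% complication rate:

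| Odds ratio per second | Uniform over 3–4 s | Half at 3 s, half at 4 s |
|---|---|---|
| 2 | 14% | 34% |
| 3 | 28% | 66% |

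This is low power. Nothing in the restriction biases the association.

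**4. If biopsies were pooled.** For an exposure that varies between biopsies, the variance inflation depends on intra-patient correlation in both exposure and outcome: 1 + (m − 1) × ρx × ρy. With m = 2.5 and both correlations 0.3 (assumed), this is 1 + 1.5 × 0.09 = 1.135, and 2 × [1 − Φ(1.96/√1.135)] = 6.6% instead of 5%. Simulated error at correlations 0.3, 0.5 and 0.8 is 5.7%, 6.5% and 9.7% for two biopsies per patient, and 6.3%, 7.7% and 14.4% for three. The excess is modest unless the correlation is high.

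**The case against.** **Time of biopsy is not shown to be operation duration.** The article lists the times of TBCB, TBLB and the operation separately, and recording a duration after the checks does not prove that haemostasis is counted in it. This is fair, and it is why the size and sign must be left open. But none of these times has a stated start or stop point and no onset time is listed, so the article offers no protection either.

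**Not every complication can act this way.** Infection, acute exacerbation and delayed events cannot lengthen a finished procedure, and Level 1 bleeding needs suction only. This stands. The point is confined to immediate bleeding and pneumothorax.

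**The percentages rest on invented inputs.** Correct. They show only that shifts of a third to five-sixths of an SD (2/6 to 5/6) are readily detected. They do not predict this trial. The protocol also speaks of a relationship and does not claim causation.

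**Unit and model may be settled elsewhere.** An article condenses the full protocol, so their absence is not in itself a fault. This stands.

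Two stronger readings are tempting and not supported:
- A reader might infer that several biopsies per patient will be tested as independent. The article does not say so. It can be read as one record of bleeding, pneumothorax and duration per technique per patient. A design effect worked out for a patient-level factor would also overstate the problem for freezing time and specimen size, which vary between biopsies.
- A reader might infer that freezing time is fixed and its analysis therefore distorted. The text gives a range and the actual freezing time is collected. A narrow range costs power and limits the conclusion to that window, but does not bias it.

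**Conclusion.** The point holds in a limited form. The association between biopsy time and immediate bleeding or pneumothorax can run backwards, because the event can lengthen the procedure through haemostasis or shorten it through the continuation rule, and the listed data contain no onset time. Size and direction cannot be derived from the document.

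For freezing time, the reservation is low information within 3–4 s. For repeated biopsies, it is only that Mann-Whitney U and chi-square assume independent observations and would not suit biopsies pooled across patients.

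The conclusion rests on the data list in the article being complete as regards timing. If the full case report form already records biopsy and event times, only the analysis wording remains to be settled. Secondary end points alone are affected; the primary comparison and the sample size are not.

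**What to change.** 1. **Data.** Define the start and stop of each recorded time. Add the clock time of each biopsy, the onset of any immediate event, and the time spent on haemostasis.
2. **Immediate events.** Analyse per biopsy, linking each event to the biopsy just taken. Exposures are the elapsed time before that biopsy (excluding haemostasis), its freezing time and its specimen size. Use logistic GEE or a mixed model clustered by patient and adjusted for biopsy number.
3. **Events that cannot be tied to one biopsy,** as may happen with pneumothorax: analyse per technique per patient. Keep delayed events at patient level.
4. **Avoid** comparing time to first complication with full duration between groups.
5. **Freezing time.** Report the association descriptively with a confidence interval, and state that it applies only within 3–4 s. No change to the freezing time or to the continuation rule is proposed.

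**Cost.** A few case report form fields, revised analysis wording and a slightly more complex model. Linking bleeding to a cryobiopsy should be easy, since the airway is already inspected after each freeze; pneumothorax is harder to attribute. The article reports one patient enrolled, so if that is still close to the position, the fields can be in place for nearly everyone. Onset times not recorded at the procedure cannot be recovered later.
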